## Abstract

**Background:**

Care for patients with heart failure (HF) causes a substantial load on health care systems where a prominent challenge is the elevated rate of readmissions within 30 days following initial discharge. Clinical professionals face high levels of uncertainty and subjectivity in the decision-making process on the optimal timing of discharge. Unwanted hospital stays generate costs and cause stress to patients and potentially have an impact on care outcomes. Recent studies have aimed to mitigate the uncertainty by developing and testing risk assessment tools and predictive models to identify patients at risk of readmission, often using novel methods such as machine learning (ML).

**Objective:**

This study aims to investigate how a developed clinical decision support (CDS) tool alters the decision-making processes of health care professionals in the specific context of discharging patients with HF, and if so, in which ways. Additionally, the aim is to capture the experiences of health care practitioners as they engage with the system’s outputs to analyze usability aspects and obtain insights related to future implementation.

**Methods:**

A quasi-experimental design with randomized crossover assessment will be conducted with health care professionals on HF patients’ scenarios in a region located in the South of Sweden. In total, 12 physicians and nurses will be randomized into control and test groups. The groups shall be provided with 20 scenarios of purposefully sampled patients. The clinicians will be asked to take decisions on the next action regarding a patient. The test group will be provided with the 10 scenarios containing patient data from electronic health records and an outcome from an ML-based CDS model on the risk level for readmission of the same patients. The control group will have 10 other scenarios without the CDS model output and containing only the patients’ data from electronic medical records. The groups will switch roles for the next 10 scenarios. This study will collect data through interviews and observations. The key outcome measures are decision consistency, decision quality, work efficiency, perceived benefits of using the CDS model, reliability, validity, and confidence in the CDS model outcome, integrability in the routine workflow, ease of use, and intention to use. This study will be carried out in collaboration with Cambio Healthcare Systems.

**Results:**

The project is part of the Center for Applied Intelligent Systems Research Health research profile, funded by the Knowledge Foundation (2021-2028). Ethical approval for this study was granted by the Swedish ethical review authority (2022-07287-02). The recruitment process of the clinicians and the patient scenario selection will start in September 2023 and last till March 2024.

**Conclusions:**

This study protocol will contribute to the development of future formative evaluation studies to test ML models with clinical professionals.

**International Registered Report Identifier (IRRID):**

PRR1-10.2196/52744

## Introduction

Care for patients with heart failure (HF) causes a substantial load on the health care system. One of the prominent challenges associated with HF care is the elevated risk of readmissions within 30 days following initial discharge [1]. While this readmission risk underscores that patients receive life-saving care, it also encompasses implications of health care costs, patient’s stress, and the impact of socioeconomic determinants on care outcomes [2]. The risk of readmission due to the worsening of HF symptoms is heightened by inappropriate treatment strategies, infectious complications, or prematurely executed discharges. Therefore, readmissions can be reduced by taking steps both during admission and hospitalization and post discharge to ensure compliance with care plans and improved treatment outcomes.

In current practice, clinicians make expert decisions, weighing in the probability of readmission of a patient by evaluating clinical data such as a patient’s medical history, medication list, laboratory tests as well as social factors [3]. However, the process of assessing a patient’s readiness for discharge introduces an element of subjectivity and uncertainty. Questions surrounding the probability of readmission emerge, prompting deliberation on optimal timing for discharge—whether immediately or with a slight delay. Additionally, the patient’s social context plays a critical role; decisions must be made regarding the suitability of home care versus outpatient clinic assignment.

In pursuit of curbing health care costs and mitigating uncertainty novel risk assessment tools, often in the form of predictive models have been developed. Drawing upon statistical, conventional machine learning (ML), and deep learning methodologies, these tools are designed to identify patients at risk of hospital readmission [4-6]. Leveraging risk indicators such as age, illness severity, prior hospitalizations, and other factors, these models predict the likelihood of readmission within a specific time frame. Preventive approaches can then be developed and applied to target the identified high-risk patients. The profound potential for cost savings within the health care domain has fueled substantial interest in rigorous testing and validation of similar models, underscoring the imperative of optimizing patient care while securing resource efficiency.

In this project, our objective is to evaluate the applicability and potential benefits of a previously established ML model for predicting unscheduled readmission of patients with HF within 30 days after discharge from medical care [5]. This model has been further fine-tuned and tailored for practical integration and usage within clinical settings [3,7], encompassing the identification of potential barriers and enablers for implementing a clinical decision support (CDS) tool presenting the model output for clinical use. Refinement also encompassed the augmentation of the model with interpretability features and a comprehensive exploration of the optimal timing and manner in which the model’s findings should be presented to users within the clinical domain [7]. The primary aim of the study outlined in this protocol is to investigate how the developed CDS tool alters the decision-making processes of health care professionals in the specific context of discharging patients with HF, and if so, in which ways. Additionally, the aim is to capture the experiences of health care practitioners as they engage with the system’s outputs to analyze usability aspects and obtain insights related to future implementation.

## Methods

### Study Design

The design of this study used the principles of Template for Intervention Description and Replication [8] to support clarity of the description of the intervention and the replicability of its implementation. This study has a quasi-experimental design with a randomized controlled crossover assessment of 2 groups of physicians and nurses working in pairs. This study will be conducted within the health care settings of 1 region in Southern Sweden. The 2 groups will be presented with patient scenarios using purposeful sampling [9] on which they are to make decisions on subsequent care plans and treatment strategies.

### HF Care Setting

An HF patient’s referral to the hospital can occur through the emergency department, primary care, or home care services. Upon arrival, the patient is allocated to one of the medical departments within either of 2 hospitals in the included region possessing specialized cardiology units. Once admitted, a comprehensive care plan is made, considering the patient’s symptoms, prior diagnoses, and relevant test results. This care plan also includes decisions regarding the appropriate timing for discharge. Within the framework of this study, this in-patient scenario, as detailed in a prior work [3], serves as the setting for HF care in which our investigation into the application of the CDS model takes place.

### Preparation for This Study

#### CDS Model

The model is based on comprehensive retrospective electronic health data in a Swedish region [10]. The cohort used for the development consisted of patients diagnosed with HF according to the *ICD-10* (*International Statistical Classification of Diseases, Tenth Revision;* I10.0, I42, I43, and I50), were residents, and receiving care in the region. The patients included were aged ≥40 years and had at least one admission after being diagnosed with HF between January 1, 2017, and December 31, 2019. All-cause hospitalization was considered. For each admission in the cohort, all patient’s previous admissions within 5 years were considered from the time of admission as the medical history of the patient (look back period); these admissions are not considered as events in this study but were used only as historical data.

Besides demographic information, variables were collected out of electronic health data related to different categories. These categories can be detailed as follows: comorbidities in which patient conditions related to HF are traced back, for example, hypertension, diabetes, chronic kidney disease, and atrial fibrillation. Diagnoses (including procedures) and medications in the electronic health data system were represented according to standard schemas: *ICD-10-SE* (*Swedish version of the 10th revision of the International Classification of Diseases*) and Anatomical Therapeutic Chemical codes, respectively. Laboratory results were also used, including specific features for some laboratory tests, such as N-terminal prohormone of brain natriuretic peptide, sodium, potassium, ferritin, and estimated glomerular filtration rate. Variables were defined to indicate the level of abnormality in the obtained results of these laboratory tests. Following clinical feedback on model development, features associated with a patient’s vital signs collected during the admission such as weight, heart rate, and blood pressure were also considered.

A conventional ML model was developed with *CatBoost*, which resembles gradient-boosting decision trees. The *CatBoost* model makes predictions using a series of decision trees, representing an explainable model [11]. In this study, the *CatBoost* python package (version 1.0.4) was used. The model was trained using a stratified 10-fold cross-validation, such that the training data were further divided into 10 parts where 90% (14,069) of data were used for training and 10% (1842) used for validation. Evaluation of the performance is based on commonly used performance measures such as sensitivity, specificity, *F*_1_-score, receiver operating characteristic curves, the area under the receiver operating characteristic curve, and the area under the precision-recall curve. The performance of the model is presented in a retrospective ML study [7].

The Shapley Additive Explanations (SHAP) technique was adopted to provide more details behind the model decision regarding important features for readmission prediction [12]. SHAP works as a model-agnostic explanation tool and provides local (ie, patient-specific) as well as global explanations (ie, across patient cohorts). SHAP was used to compute explainability outputs for the selected patient scenarios, which were later used as input to the CDS tool. For each prediction, the most important features were listed that were positively or negatively driving toward the readmission risk. The explanations provided were assessed by physicians for clinical relevance.

#### Stakeholder Study

To prepare for the experiment, an interview study was performed to determine the potential barriers and facilitating factors for the implementation of the CDS tool. In total, 12 interviews with stakeholders were performed in a Swedish health care organization consisting of 2 hospitals, primary care, and partial home care. The views on the CDS tool were collected from different roles such as medical process leaders, medical specialists in cardiology, specialist nurses, physiotherapists, home care physicians, home care nurses, and administrative roles [3]. Interviews were transcribed and thematically analyzed to condense and categorize content.

#### Explainable Artificial Intelligence Design Process

A design process was carried out to create the user interface of the CDS tool. The initial phases included expert interviews, care process observations, and literature searches about the design of explainable artificial intelligence (AI) systems. There are several design problems to address in creating an interface for such a decision support system, for example, to understand who the intended users are and their needs, what information flows the system shall interact with, and in what part of the care process such information is relevant [13]. Therefore, an iterative design process was adopted, to move forward step by step, while generating and testing different design ideas.

Initial usability tests were conducted after generating a set of low-fidelity prototypes. In total, 5 clinicians (3 physicians and 2 nurses) were individually testing the different prototypes over recorded video calls. The tests evaluated if the prediction score and the explanation presented in the prototypes were understandable, and how clinicians perceived this information given the situation of an AI-model as the source. The tests gave important information on which language to use and what to display in the interface, which was the focus of the next iteration. The initial usability tests further raised questions about where this tool might be needed and who the users could be. Consequently, additional care process observations were made, which led to some changes to the definition of the target users and the place of potential implementation.

All usability test data were analyzed, categorized, and used as input for the further development of the prototype. Thereafter, additional usability testing was performed, following the same procedure as previous tests, however, focusing on exploring how to present more detailed information. Another 5 clinicians (three of them participated in the first usability tests) tested these prototypes over video calls. The outcome of this second round of usability tests was used as input to another design update before a high-fidelity prototype was created. This prototype was tested with 4 clinicians (2 physicians and 2 nurses who also participated in the previous tests).

As the last step of the prototype development, a series of design workshops were conducted with user experience resources, to finalize the prototype and set the details, before a smaller usability test was performed with 2 clinicians (1 physician and 1 nurse). Their input led to some minor interface changes, and now the development of the CDS tool could begin.

#### Scenario Creation

From the same data set used to develop the CDS model, 20 patients were selected to constitute the target population in this study by using stratified random sampling. The stratification was made to ensure that there are equal amounts of readmitted patients and control patients. For each of these 20 patients, scenarios comprising narrative reports and clinical data describing demographics, and clinical events and outcomes, including potential readmittance, were recreated retrospectively based on real patient historical data from the regional database of electronic health data.

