### Experimentation and Data Collection

The experiment simulates the decision-making process of a patient’s discharge, further treatments, and care plan, based on real historical data. Patient data for model output are preloaded into the CDS model. The participants will be randomly paired with 1 physician and 1 nurse in each pair, reflecting the real-world setup in the decision-making regarding the patient’s potential readmission (Figure 1). Pairs will then be randomly assigned into test (n=3) and control (n=3) groups using simple randomization with stratification. The pairs in the test group will be given 10 scenario descriptions, patient electronic health record (EHR) data, and the CDS model output based on each of the 10 patients. The pairs in the control group will be given the same 10 scenario descriptions and EHR data but not the CDS model output. After making decisions based on the 10 scenario descriptions the test group and the control group will switch roles and 10 new scenario descriptions will be given to the groups, again with and without the CDS model output.

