**Impact on decision-making**			
	Decision consistency	To explore decision consistency between the users and the CDS^a^ model to research whether having the CDS model increases uniformity among the decisions taken compared to decisions without the model.	Comparing the taken decisions: Between the CDS model output and the test group to assess the extent of how much the users agreed with the model output. Between test and control groups to assess similarity in decisions taken with and without the model output. Potential decisions: To discharge, with x, y, and z treatment. Move to another department (which?). Take additional tests for an extended investigation. To send a referral or follow-up at outpatient clinical, primary care, or home care. To stay for some more days.
	Decision quality	To explore whether the CDS model could improve decisions.	Comparing decisions taken by the test group with: Historical data—what decision was actually taken for the patient and what event followed afterwards. Control group’s decisions on the same patients to control the influence of the experiment and set up over the decisions taken: do decisions differ from the test group and the historical data?
	Work efficiency	To explore performance changes due to using the CDS model output.	Measuring speed of decision-making for both test and control groups. Comparing the average speed between groups with and without CDS.

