## Discussion

### Principal Findings

This study focuses on the ML model for predicting unscheduled readmission of patients with HF within 30 days of discharge [5]. The purpose of the study described in this protocol is to assess the impact of this ML model on decision-making by health care professionals and to capture their experiences in using the model.

A quasi-experimental study shall be conducted with clinicians using the model and results shall be compared against a control group. Throughout the experiment, the researchers shall observe the decision-making process, take measurements, and collect feedback. Such knowledge shall increase an understanding of the potential impact on the decision-making, usability, perceived value if such a model is deployed, and willingness to use such tools in the future. Furthermore, this study will give practical insights into the factors that will potentially influence implementation that could be further used in the implementation process. In addition, concrete outcomes’ measures are suggested which can assist in future developments of similar models.

This study has several limitations. First, although the CDS model output shall be provided as a digital interface, the system is not in this version integrated with EHR and it will not be possible to check the actual impact of the CDS model on the workflow. Second, the samples of admissions will be selected using stratified sampling where subgroups will be created for readmission labels assigned to patient encounters. The readmission rate in our data set is 21% (3334 out of 15,911 admissions), thus the chance to obtain enough examples where the readmission label is true will be very low. Accordingly, stratification will be used to divide the population data into 2 subgroups before sampling, then select 10 cases having true as a value for readmission label. Third, this study shall not assess the impact of the use of the model on the cost-efficiency or resource planning. Fourth, the presence of a researcher (an observer) in the computer room while clinicians assess the patient scenarios might influence the results.

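### The 20 scenarios come from the model's own development data, so the displayed risk scores are probably in-sample for most of them and favour the tool on decision quality

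*Protocol article*

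**What the plan says.** All references are to the protocol article.

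- **Source of the scenarios** (Methods, Scenario Creation): "From the same data set used to develop the CDS model, 20 patients were selected to constitute the target population in this study".
- **How they are sampled** (Discussion, Principal Findings): "stratification will be used to divide the population data into 2 subgroups before sampling, then select 10 cases having true as a value for readmission". The readmission label is the only criterion given for dividing the data before sampling.
- **How the model was fitted** (Methods, CDS Model): "The model was trained using a stratified 10-fold cross-validation", with "90% (14,069) of data were used for training and 10% (1842) used for validation".
- **Size of the data set** (Discussion, Principal Findings): "The readmission rate in our data set is 21% (3334 out of 15,911 admissions").
- **How the output reaches clinicians** (Methods, Experimentation and Data Collection): "Patient data for model output are preloaded into the CDS model". Under CDS Model, SHAP outputs for the chosen scenarios are computed and fed to the tool.
- **Outcomes** (Table 1, Impact on decision-making): decision quality compares test-group decisions with the historical record, namely "what decision was actually taken for the patient and what event followed afterwards", and with the control group's decisions on the same patients. Decision consistency includes a comparison with the model "to assess the extent of how much the users agreed with the model output".

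Four limitations are listed under Principal Findings. The stratified sampling is one of them. The overlap between scenario patients and development data is not.

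**The concern.** A flexible model fits the records it was trained on better than records it has not seen. If a scenario patient's readmission label was used in the fit, the displayed risk already carries some information about that patient's recorded outcome. A clinician who follows it is then moved towards the recorded event more often than would happen with a new patient.

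The crossover does not cancel this. According to Experimentation and Data Collection, each set of 10 scenarios is judged by one group with the model output and by the other without it. Only the CDS condition receives the in-sample help, so the advantage falls directly on the contrast between conditions. The Abstract describes the control scenarios as a different set of 10. On that reading too, the output appears only on the CDS side.

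At stake is whether a favourable decision-quality result can be carried over to patients the model has not met. With 20 scenarios and a mainly descriptive analysis, the advantage cannot be separated out afterwards.

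**Working it through.** **Inputs.** Training records 14,069 and validation records 1842 (CDS Model). Total admissions 15,911, of which 3334 were readmitted (Principal Findings). Scenarios 20, of which 10 readmitted (Scenario Creation, Principal Findings).

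**1. Reproduce the article's own figures.**
- Readmission rate: 3334 / 15,911 = 20.95%, which agrees with the stated 21%.
- Training plus validation: 14,069 + 1842 = 15,911, exactly the stated total.
- Remainder for a separate held-out set: 15,911 − 15,911 = 0.

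**2. Check the stated split.** 14,069 / 15,911 = 88.4% and 1842 / 15,911 = 11.6%. One tenth of 15,911 is 1591, not 1842. The counts and their 90%/10% labels therefore do not agree, and the counts do not cleanly describe ten equal folds of the full data.

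**3. How many scenarios are in-sample?** This depends on which fit produced the displayed scores, which the article does not say.
- *The counts are one fixed split, and the model fitted on the training part is used.* Expected scenarios in training = 20 × 14,069 / 15,911 = 17.7. The chance that none of the 20 falls there is C(1842, 20) / C(15,911, 20), about 1.7 × 10⁻¹⁹. This treats admissions as the sampling unit and ignores the 10/10 stratification by label. If both parts have a similar readmission rate, the expected number hardly changes.
- *The final model was refitted on all data after cross-validation.* All 20 are in-sample.
- *Each scenario was scored out of fold, or by a model refitted without the 20 patients.* No scenario admission is in-sample. Neither procedure is described.

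The data are counted in admissions, while the scenarios are patients. Unless folds were grouped by patient, which is not stated, another admission of a scenario patient could also sit in the training part.

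**4. Which outcomes are exposed?**
- *Decision quality:* exposed, because the reference includes the later event, and readmission is what the model was fitted to predict.
- *Agreement with the model:* decisions are compared with the output, not with the true event, so a link is possible but indirect.
- *Confidence and perceived reliability:* possible, if in-sample scores and explanations look more convincing. No feedback to clinicians on whether the model was right is described.
- *Speed, workflow integration, ease of use:* no link is apparent.

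**5. Size.** It cannot be computed, because the article refers model performance to a separate study. As arithmetic only, every 5 percentage points of optimism in accuracy means 20 × 0.05 = 1 more scenario with a correct score. On assumed accuracies, 60% to 70% on new patients gives 12 to 14 of 20 correct, and 80% to 95% in-sample gives 16 to 19. The gap would then be between 16 − 14 = 2 and 19 − 12 = 7 scenarios. These accuracies are not in the article. The counts describe the model, not the clinicians' decisions, which Table 1 does not reduce to two options.

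**The case against.** The strongest reply is that in-sample use is inferred. Under 10-fold cross-validation every record is scored once by a model that did not train on it, so out-of-fold scores could exist for all 20 scenarios. The article does not say which fit feeds the tool, and preloading patient data does not settle it. The wording under CDS Model also speaks of the training data being divided further, which hints at an earlier split, and 1842 is not a tenth of the total. This stands as a limit on certainty. It does not remove the point: the counts leave no records for an earlier hold-out, sampling is from the whole data set, and no out-of-fold procedure is described.

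A reader might go further and infer that every scenario is certainly in-sample, or that every outcome is biased towards the tool. The documents support neither. Under one fixed split the expected share is about 88%, and several outcomes in Table 1 do not depend on whether the displayed risk is right.

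It can also be said that this is an exploratory, mainly descriptive study that does not set out to estimate model accuracy. That is true and limits how much rests on any one result. Decision quality is nevertheless a named key outcome, and its comparison with the recorded event depends on the accuracy of what clinicians are shown.

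Finally, an article condenses a fuller protocol. That could explain silence on out-of-fold scoring, but the source of the scenarios is stated outright.

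**Conclusion.** The point holds in a limited form. The scenario patients come from the development data, and the stated counts use up all 15,911 admissions. Followed as written, the plan probably shows clinicians in-sample scores and explanations for most scenarios: about 17.7 of 20 under one fixed split, and all 20 after a refit on all data. The expected effect is a bias towards the tool in the comparison of decision quality with and without CDS.

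This rests on two assumptions: that the displayed output comes from the fitted development model and not from out-of-fold scores, and that this model fits its training records better than new ones. The direction is an expectation over scenarios, not a certainty for each of 20 cases. Effects on agreement, confidence and perceived reliability are possible but not shown. A reader might take the illustrative gap of 2 to 7 scenarios as an estimate. It is not one, since it rests wholly on assumed accuracies.

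**What to change.** Before data collection:

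1. Refit the same CatBoost specification after removing all admissions of the 20 scenario patients, not only the index admission. Alternatively, use out-of-fold scores with folds grouped by patient.
2. Regenerate the 20 risk scores and SHAP outputs from that fit.
3. State under Scenario Creation that the displayed outputs come from a model that did not see these patients.
4. Reconcile the 90%/10% labels with the counts 14,069 and 1842 under CDS Model, and say how the folds were formed.

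If the displayed scores already meet this condition, one sentence saying so is enough. If they do not and no refit is made, list the overlap under Principal Findings as a limitation on decision quality.

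The cost is one refit, 20 regenerated outputs and a short text change. The physicians' check of the explanations for clinical relevance may have to be repeated, and the displayed accuracy may look less favourable.

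### Agreement with the model output is defined only for the aided pairs and is not split by whether the output was right, so it may not separate helpful influence from over-reliance

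*Protocol article*

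**What the plan says.** **Sampling.** The Protocol article (Methods, Scenario Creation) states: "From the same data set used to develop the CDS model, 20 patients were selected". It adds: "The stratification was made to ensure that there are equal amounts of readmitted patients and control patients". The limitations in Principal Findings repeat that the label alone defines the two strata: "stratification will be used to divide the population data into 2 subgroups before sampling". No section sets how many of the 20 displayed outputs should be right or wrong.

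**Measure.** In Table 1 (Outcome Measures) the first comparison under decision consistency is: "Between the CDS model output and the test group to assess the extent of how much the users agreed with the model output". A second comparison looks at how similar the decisions of the test and control groups are. Decision quality is a separate row. It sets the test group's decisions against the historical decision and the later event, and against the control group's decisions on the same patients. Neither row distinguishes scenarios with a correct output from those with an incorrect one.

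**Analysis.** The Data Analysis section says that the quantitative part will be mainly descriptive.

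**The concern.** The primary aim is to learn whether, and in which ways, the tool alters decisions. Agreement among aided pairs does not show that by itself. Where the output is right, experienced clinicians may have reached the same decision without it. Where the output is wrong, agreement is the warning sign that evaluations of decision support look for. A single rate mixes the two.

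Two ingredients are missing from the stated measure. One is the reference level: how often unaided pairs land on the same answer as the hidden output. The other is the split by correctness. The sampling adds a further limit. Wrong outputs are the scenarios that reveal over-reliance, and their number is not controlled. If few occur, later analysis cannot supply them.

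**Working it through.** **Inputs from the article**
- 20 scenarios, 10 with a true readmission label (Scenario Creation; Principal Findings).
- 6 pairs, 3 per group. In Methods both groups receive the same scenarios, so each scenario is judged by 3 aided and 3 unaided pairs (Experimentation and Data Collection). The Abstract speaks of other scenarios for the control group. This check follows Methods and Table 1.
- 3334 readmissions in 15,911 admissions (Principal Findings).
- Model sensitivity and specificity: not given. Assumed equal and varied.

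**Step 1: the plan's own figure.** 3334 / 15,911 = 20.95%, which reproduces the stated 21%. A simple random draw of 20 would contain 20 × 0.2095 = 4.2 readmitted patients on average, and at least 10 with probability 0.4%. Stratifying on the label is therefore justified in itself.

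**Step 2: the label does not control wrong outputs.** Let acc be the assumed accuracy in both label groups. The expected number wrong is 20 × (1 − acc), and P(none wrong) = acc^20. Aided pair decisions on wrong outputs number 3 × the expected count, out of 20 × 3 = 60.

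| Assumed acc | Expected wrong of 20 | 95% range | P(none of 20) | Aided decisions on wrong outputs |
|---|---|---|---|---|
| 70% | 6 | 2 to 10 | 0.1% | 18 |
| 80% | 4 | 1 to 8 | 1.2% | 12 |
| 90% | 2 | 0 to 5 | 12% | 6 |
| 95% | 1 | 0 to 3 | 36% | 3 |

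**Step 3: one agreement rate, several behaviours.** With w wrong outputs, overall agreement = [(20 − w) × agreement on right outputs + w × agreement on wrong outputs] / 20. Take w = 4:
- Indiscriminate (80% on right, 80% on wrong): (16 × 0.80 + 4 × 0.80) / 20 = 80%.
- Perfect discrimination (100%, 0%): (16 × 1 + 4 × 0) / 20 = 80%.
- Following every wrong output (75%, 100%): (16 × 0.75 + 4 × 1) / 20 = 80%.

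If unaided pairs also match the hidden output 80% of the time overall, the overall difference is 0 and the rate shows no net influence.

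**Step 4: what decision quality adds.** Suppose decisions are scored as high or low risk against the outcome. The share correct is then [(20 − w) × agreement on right + w × (1 − agreement on wrong)] / 20. The three patterns give (12.8 + 0.8) / 20 = 68%, (16 + 4) / 20 = 100% and (12 + 0) / 20 = 60%. So quality can separate them, given a common scoring. Table 1 states no such scoring, and an overall aided-versus-unaided difference in quality can still hide a loss on wrong outputs behind a gain on right ones.

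**Step 5: precision.** With 4 wrong outputs there are 12 aided decisions. At a proportion of one half, the naive 95% half-width is 1.96 × √(0.25 / 12) = 0.28. That treats decisions on the same scenario as independent, so it is optimistic. Results on wrong outputs will be descriptive at best.

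**The case against.** A reader might infer that the study has no means of telling helpful influence from over-reliance. The documents do not support that:
- Decision quality uses the later event and unaided pairs on the same patients, and Step 4 shows that it carries relevant information.
- Decision consistency includes a test-versus-control comparison. It shows whether decisions differ, though not whether they moved toward the output.
- Think-aloud recordings, the log of information requests and the ratings of confidence and of how far the output helped all bear on reliance. It would be wrong to say that only interview opinion covers it.
- The outcome and output are known for every scenario, so the split needs no new data. The article does not rule it out, and a fuller analysis plan may contain it.

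Nor does the article say that higher agreement will be read as benefit. Improvement belongs to the decision-quality row.

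A reader might also infer that wrong outputs will be unusually scarce because the scenarios come from the development data. The training and validation counts do add up to the whole data set (14,069 + 1842 = 15,911), so no separate held-out set is described. But the model was cross-validated, and nothing says whether the displayed predictions are in-sample. Scarcity is possible, not established.

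Finally, a displayed risk is not plainly wrong because one patient had the other outcome, and the listed decisions have several categories. Right and wrong need definitions. That objection stands and shapes the fix, but it applies equally to the agreement measure already planned.

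What remains is that the stated measure lacks the unaided reference and the split, and that the number of wrong outputs is uncontrolled.

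**Conclusion.** The point holds in a limited form. As stated, agreement with the output may reflect benefit, no influence or over-reliance, and decision quality resolves this only in part. The ambiguity in Step 3 is arithmetic and needs no assumption beyond the illustrative 4 wrong outputs. The counts in Step 2 rest on assumed accuracies, equal in readmitted and control patients, because the article gives none. At 70% the study would almost certainly contain wrong outputs. At 95% there is about a one-in-three chance of none.

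This is an inexpensive improvement to an exploratory, descriptive study and does not invalidate the design.

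**What to change.** **Before the decisions are seen**, fix a cut-off that turns the displayed risk into high or low, and a mapping of the possible decisions to high or low risk. The study team should choose both; this review proposes neither.

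**Then report:**
1. For each scenario, the share of with-CDS pairs agreeing with the output minus the share of without-CDS pairs agreeing with the same hidden output.
2. That difference, and decision quality, separately for scenarios where the output matched the 30-day outcome and where it did not.
3. The number of scenarios in each group, and whether the displayed predictions are out-of-fold.
4. If few or no outputs were incorrect, a plain statement that over-reliance could not be assessed.

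**Cost.** No new data and no change to the experiment: outputs, outcomes and same-patient controls are already planned. The work is two definitions and a table. With 3 pairs per condition, each scenario's share moves in steps of one third, so the results stay descriptive.

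**Optional.** Scenarios could be drawn by output correctness within each label, which would guarantee some wrong outputs. This is a trade-off. It changes the error rate that participants experience and may shift the interview findings on reliability, confidence and intention to use. It may also mean rebuilding scenarios, since Scenario Creation describes them as already made.
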